### Sample size

The sample size was calculated using the G*Power 3.1.9.4 statistical software according to the main objective. Considering a confidence level of 95%, a power of 80% and an effect size *d* = 0.85, 25 individuals per group are needed to detect a significant difference in the median frequency of self-injurious behaviors with the two tailed Mann–Whitney U test. Assuming a proportion of lost in the follow-up of 15%, then the study would have to start with 29 individuals per group.

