### Statistical analysis

To describe the sociodemographic characteristics of the patients in the two groups, absolute and relative frequencies (%) will be used for the qualitative variables, and the mean and standard deviation will be used for the only quantitative variable (age) if it presents a normal distribution according to the Shapiro–Wilk test. In case of presenting a non-normal distribution, the median and the interquartile range will be computed.

To compare the sociodemographic characteristics between the groups, the chi-square or Fisher’s exact test will be used for the qualitative variables, and the student’s t-test or the Mann–Whitney U test will be computed for the quantitative variable.

For all patients and at each follow-up moments, the difference between the frequency of each suicidal behavior and the baseline frequency will be calculated. Then it will be evaluated if these differences follow a normal distribution (Shapiro–Wilk test). In this case, the mean differences for each behavior between both groups will be compared using the t-Student test. Otherwise, the medians will be compared with the Mann–Whitney U test. The *p*-values obtained will be corrected according to the Bonferroni criterion.

To assess whether the change in emotional regulation mediates the change in the frequencies of each suicidal behavior, the difference between the value of the DERS scale at the last follow-up and the baseline will be calculated, and the Sobel test will be used on a regression model whose dependent variable will be the difference in the frequency of each behavior and the independent variable will be the treatment. Previously, the probability distribution of the quantitative variables will be evaluated and it will be considered whether it is necessary to carry out any transformation of data to guarantee compliance with the assumptions of the regression model.

Both for the frequencies of the different suicidal behaviors and for the DERS scale, the missing values will be imputed according with the multiple imputation method using chained equations (MICE) with appropriate models for each variable to be imputed, considering sociodemographic characteristics, the hospital of recruitment and the baseline measurements of frequencies and DERS scale as independent variables.

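### Multiple imputation is joined to a normality-gated choice of t-test or Mann–Whitney test, and the procedure as stated does not lead to one pooled primary result

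*Protocol article*

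**What the plan says.** All the analysis rules are in the Statistical analysis section of the protocol article.

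- **Outcome.** For every patient and every follow-up visit, the change from baseline in the frequency of each behaviour is calculated.
- **Gate.** "Then it will be evaluated if these differences follow a normal distribution (Shapiro–Wilk test".
- **If normal.** "the mean differences for each behavior between both groups will be compared using the t-Student test".
- **If not normal.** "Otherwise, the medians will be compared with the Mann–Whitney U test".
- **Multiplicity.** The p-"values obtained will be corrected according to the Bonferroni criterion".
- **Missing data.** "the missing values will be imputed according with the multiple imputation method using chained equations (MICE", with models "considering sociodemographic characteristics, the hospital of recruitment and the baseline measurements of frequencies and DERS scale as independent variables".

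The section does not say whether the Shapiro–Wilk check uses observed data or each imputed dataset, or what happens if imputed datasets disagree.

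The Sample size section bases the calculation on the non-normal branch: "Considering a confidence level of 95%, a power of 80% and an effect size" of 0.85, "with the two tailed Mann–Whitney U test". It assumes 15% loss to follow-up.

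**The concern.** Multiple imputation produces several completed datasets. The usual way to combine them needs the same estimate and its variance from each one. The plan instead prescribes a procedure whose form depends on the data. One imputed dataset may pass Shapiro–Wilk and yield a mean difference, while the next fails and yields a rank statistic, and the two are not on the same scale. Even if every dataset led to the Mann–Whitney test, its standard output is U and a p-value, with no estimate and standard error to pool.

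An analyst who follows the text faithfully must therefore add a rule or change the test. If that is done after the data are seen, the choice can affect the primary p-value. Two easy improvisations, testing one imputed dataset or summarising the p-values by their median, do not carry the imputation uncertainty properly.

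**Working it through.** **1. The plan's own sample size.** Inputs from the Sample size section: d = 0.85, two-sided 5%, power 80%.

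- Normal approximation: n = 2(1.96 + 0.84)²/0.85² ≈ 21.7, so 22 per group.
- Noncentral t: 23 per group.
- Mann–Whitney, normal parent (asymptotic relative efficiency 3/π): 24 per group.
- Mann–Whitney, minimum efficiency 0.864: 27 per group.

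The stated 25 is reproduced to within 2 patients. The stated 29 matches 25 × 1.15 = 28.75, rounded up; 25/0.85 = 29.4 would round up to 30. The sizing confirms that the Mann–Whitney branch is the one the plan expects to use.

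**2. How much is imputed.** 29 × 0.15 = 4.35 patients per arm are expected to have missing outcomes, leaving 29 × 0.85 = 24.65 observed. A change score for every patient then exists only after imputation.

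**3. What pooling needs.** With m imputed datasets, estimates Qₖ and variances Uₖ: pooled estimate = mean of Qₖ; W = mean of Uₖ; B = variance of the Qₖ; total variance T = W + (1 + 1/m)B.

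- t-test branch: Q is the mean difference and U its squared standard error, so it pools directly.
- Mann–Whitney branch as stated: U statistic and p-value only. There is no Q on an effect scale and no variance to enter.
- Mann–Whitney probability: Q = P(app change lower than control change) + ½P(tie), with a variance built from the row and column means of the pairwise comparisons. This pools.

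**4. How often the gate disagrees with itself.** All runs used 29 per arm, 15% missing and 20 imputations. The documents give no standard deviation or event distribution, so the data models are assumptions.

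| Simulation | Trials | Gate differs between imputations |
|---|---|---|
| Negative-binomial counts, within-arm bootstrap imputation | 1,000 | 34% |
| Skewed counts and normal data, predictive mean matching on baseline and arm | 600 per scenario | 27% to 38% |
| Further assumed distributions | 500 per scenario | 33% to 52% |

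**5. What happens under the null, nominal 5%.**

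| Rule | 600-trial runs | 500-trial runs |
|---|---|---|
| One imputed dataset | not run | 7% to 11% |
| Median of the p-values | 6.2% skewed, 8.2% normal | 6% to 9% |
| Rubin, mean difference | 4.5% skewed, 5.2% normal | not reported |
| Rubin, Mann–Whitney probability | 4.7% skewed, 5.8% normal | 5% to 7% |

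Simulation error at 5% is √(0.05 × 0.95/600) ≈ 0.9 points for 600 trials and about 1.0 point for 500. So 8.2% is a clear excess, (8.2 − 5)/0.9 ≈ 3.6 standard errors. The 6.2% taken alone is not, (6.2 − 5)/0.9 ≈ 1.3.

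**6. With a true effect (600-trial runs).** The median-p rule rejected 27.8% against 25.7% for the pooled Mann–Whitney probability with skewed counts, and 68.3% against 62.0% with normal data. Part of the shortcut's apparent advantage is its inflated error rate.

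**The case against.** The strongest reply is that this is only a missing pooling sentence. A journal article commonly leaves such detail to an analysis plan that is not shown, and the protocol proposes neither one imputed dataset nor a median p-value. That stands as far as the missing sentence goes, and its absence is not the point made here. What remains is that two rules which are written down do not combine into one result. An analysis plan faithful to both would still have to replace the gate, the test or its effect measure.

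The reply also notes that the text never says Shapiro–Wilk is run per imputed dataset. That is correct. A single check on observed changes would remove the switching, though the Mann–Whitney branch would still lack a poolable quantity.

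Two stronger readings are tempting and are not supported:

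- A reader might infer that no valid combined p-value is possible. That is wrong. The t-test branch pools directly, and the Mann–Whitney probability pools with near-nominal error.
- A reader might take as harm the share of trials whose imputation-specific p-values fall on both sides of 0.05 (16% to 44% in the 600-trial runs, 45% in the 1,000-trial run). That is ordinary between-imputation variation, and it would arise with any test.

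Finally, normality pre-testing is open to criticism without missing data too. That is a separate matter and adds no weight here.

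**Conclusion.** The point holds in a limited form. As written, imputation and the normality-gated test do not yield one pooled primary result, although such a result is within reach. The switching figure of about 27% to 52% depends on running the gate within imputed datasets. The error rates of about 6% to 11% for shortcuts, against roughly 5% to 7% with pooling, describe rules that an analyst might improvise, not rules that the protocol states. Both sets of figures rest on assumed distributions, 20 imputations and an uncorrected 0.05 threshold, whereas the protocol applies Bonferroni. The predictive-mean-matching runs included treatment arm in the imputation model, which the protocol does not list as a predictor. The ranges for shortcuts and pooling overlap slightly, so the excess should be read as a tendency of a few points at most. This should be settled before analysis; it does not undermine the design.

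**What to change.** For the primary comparison, drop the Shapiro–Wilk switch and name one effect measure with a standard error in advance. The Mann–Whitney probability, with ties counted half, stays closest to the basis of the sample size. A baseline-adjusted count regression is an alternative, but it changes the effect being estimated. Estimate the chosen measure in every imputed dataset, pool by Rubin's rules with small-sample degrees of freedom, and apply the Bonferroni correction to the pooled p-values.

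The cost is a wording change and minor programming, with no new data. The p-values will be slightly less favourable than those of an unpooled analysis, because imputation uncertainty is then counted.

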#### Secondary specific objectives

Analyze the frequency of self-injurious thoughts in the participants who receive the application with the frequency in those who do not receive the app.Establish that there is no increase in the frequency of self-injurious thoughts and behaviors in those participants who receive the application compared to the baseline levels at study onset.To explore whether the effectiveness of CALMA in reducing the frequency of self-injurious thoughts and behaviors is mediated by improved emotional regulation.Describe the levels of app engagement by the adolescent participants who used it during this study.To compare the time to psychiatric admission during the follow-up period in the participants enrolled who received the app with those participants who did not receive the app.

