### Patient eligibility

#### Subjects

Patients aged 10 to 19 who attend on as outpatient basis or have been hospitalized in Mental Health Services and who have a smartphone where the application can be installed and used are eligible to participate in the study. In addition, participants must have had suicidal behavior in the 4 weeks before entering the study. The SITBI assessment questions will be used to define suicidal behavior: suicide attempt [“made a suicide attempt (i.e., purposefully hurt yourself with at least some intent to die)?”], exhibited a suicidal gesture (Have you ever done something to lead someone to believe that you wanted to kill yourself when you really had no intention of doing so?) or self-injurious behavior (Have you ever done something with the purpose of hurting yourself without wanting to die?–for example, cutting or burning-) in the last month before entering the study (53, 54).

The participant must have plans to continue treatment in the next 3 months, have the ability to provide assent/consent for cognitive or language reasons, and the functional capacity to use the application, which will be operationally determined by a score above 30 on the Self-Care motor domain, above 10 on the Communication cognitive domain and above 14 on the Cognitive domain of Social Knowledge in the Functional Independence Measurement scale (46).

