##### Time to psychiatric admission

At follow-ups and at the final interview, participants will be asked if they have had a psychiatric hospitalization for a self-injurious behavior during the follow-up period. This measure will be used to compare time to psychiatric admission in those participants who received the intervention with those participants who did not receive the app.

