Regarding acceptability, the UEQ Data Analysis Tool offers a benchmark to classify the application in 5 categories of 6 scales: excellent, good, above average, below average and bad allowing conclusions to be drawn about the relative quality of CALMA compared to other products.^2^

To evaluate and compare the time to readmission in patients enrolled during hospitalization, a Cox regression model will be adjusted, considering the treatment of each patient as the independent variable. For this, the time elapsed from study entry to readmission (event) or to loss of follow-up or final of the study (censoring) will be calculated. In all cases, a value of *p* less than 0.05 will be considered significant. Statistical analysis will be performed with RStudio 1.4.1106.

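### The only time-to-event analysis covers readmission in patients enrolled as inpatients, while the secondary objective compares time to psychiatric admission in all participants

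*Protocol article*

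**What the plan says.** Four parts of the protocol article bear on this outcome.

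- **Secondary specific objectives.** The last objective is "To compare the time to psychiatric admission during the follow-up period in the participants enrolled who received the app", set against participants who did not receive it. Nothing limits it to inpatients.
- **Time to psychiatric admission (outcome definition).** At the follow-up and final interviews, "participants will be asked if they have had a psychiatric hospitalization for a self-injurious behavior during the follow-up period". The measure is then used to "compare time to psychiatric admission in those participants who received the intervention with those participants who did not receive the app".
- **Subjects.** Both modalities are eligible: "Patients aged 10 to 19 who attend on as outpatient basis or have been hospitalized in Mental Health Services". The Recruitment section also covers both, and treatment modality (outpatient or inpatient) is listed among the sociodemographic variables.
- **Statistical analysis.** The one time-to-event analysis reads "To evaluate and compare the time to readmission in patients enrolled during hospitalization, a Cox regression model will be adjusted", with treatment as the independent variable. For it, "the time elapsed from study entry to readmission (event) or to loss of follow-up or final of the study (censoring) will be calculated".

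The Participant timeline adds that at the day-30 and day-60 calls participants are asked about hospitalisation in the period and, if there was one, its admission date. That question is not confined to those enrolled in hospital.

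**The concern.** Between the objective and the analysis, two things change. The population goes from all participants to those enrolled while in hospital, and the event goes from admission to readmission. No analysis is given for an admission of a participant who entered as an outpatient, although the data are gathered.

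At stake is whether a stated secondary objective is answered at all. The Discussion gives a lower probability of hospitalisation as one reason why the app would matter, and an inpatient-only model cannot speak to that for the enrolled population. If the conflict is left until data are in hand, the choice of population could also be made with the results known.

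A smaller matter concerns patients in hospital at entry. They cannot be readmitted until discharged, and the article does not say how the remaining index stay is treated.

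**Working it through.** **Step 1. Set the definitions side by side.**

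| Element | Objective and outcome definition | Cox analysis |
|---|---|---|
| Population | All participants, app versus no app | Patients enrolled during hospitalisation |
| Event | Psychiatric admission (for self-injurious behaviour) | Readmission |
| Time | During follow-up (90 days) | From study entry to readmission, loss or end of study |

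The first two rows conflict, and no other section reconciles them. The third row does not conflict. This finding depends on no figure.

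**Step 2. The plan's own figure.** The article gives no event count, hazard ratio or power for this outcome. Its only sample size is for the primary objective: d = 0.85, two-sided 5%, 80% power, Mann–Whitney U, 25 per group. A normal-parent efficiency adjustment gives 24 per group, close to the stated 25. The plan's 29 matches 25 × 1.15 = 28.75; dividing 25 by 0.85 gives 29.4, or 30. The point here uses only the starting total, 2 × 29 = 58.

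**Step 3. Illustrate the loss.** Assumed, because the documents are silent: 25% admission by day 90 under usual treatment, hazard ratio 0.5, 30% of participants inpatients at entry, and the same admission risk in both modalities.

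- Control events: 29 × 0.25 = 7.25.
- App events: 29 × (1 − 0.75^0.5) = 29 × 0.134 = 3.9.
- All participants: 7.25 + 3.9 ≈ 11.1 events.
- Inpatient subset: 0.30 × 58 ≈ 17 patients and 0.30 × 11.1 ≈ 3.3 events.

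Schoenfeld power with 1:1 allocation is Φ(√(events/4) × |ln HR| − 1.96), with |ln 0.5| = 0.693.

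- All participants: √(11.1/4) × 0.693 − 1.96 = −0.81, power about 21%.
- Subset: √(3.3/4) × 0.693 − 1.96 = −1.33, power about 9%.

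**Step 4. Vary the assumptions.** With overall 90-day event rates of 10% to 40% and a hazard ratio of 0.5, power is 13% to 39% with all 58 participants, and 6% to 22% with an inpatient subset of 25% to 50%. At a 20% event rate and a hazard ratio of 0.3, it is 54% with all 58, 31% with a 50% subset and 18% with a 25% subset. For 80% power at a hazard ratio of 0.5, Schoenfeld's formula needs 66 events, more than the 58 participants enrolled.

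**Step 5. Remaining index stay.** The documents give no length of stay. If 7, 14 or 30 days remained after entry, then 7/90 = 8%, 14/90 = 16% or 30/90 = 33% of the window would be time in which readmission cannot occur. These are shares of follow-up, not estimates of bias.

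**The case against.** **The time origin.** A reader might infer that starting the clock during the index stay creates immortal-time bias, or that study entry is the wrong origin. The documents do not support that. Study entry is the usual origin in a randomised comparison and applies equally to both arms. The remaining stay would distort the hazard ratio only if it differed between arms, and nothing in the article suggests that it does. Chance imbalance is possible in a small subset under simple randomisation, but that is a reason to state how index-stay days are handled, not an error on the scale of the population mismatch. Starting the clock at discharge has its own weakness: discharge follows randomisation and the app is installed at the first interview, so that analysis conditions on a post-randomisation event.

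**Another way to reconcile.** The conflict could be removed by narrowing the objective and the outcome definition to inpatients. That would be consistent, but it would abandon the question as posed although data from all participants are being collected.

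**The illustration.** Its inputs are assumed. The subset figure takes inpatients and outpatients to have equal risk; if patients in hospital at entry are at higher risk, the subset holds more than 30% of the events and the loss is smaller. This stands.

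**The stakes.** This is the last of the secondary objectives. The primary analysis and the safety procedure are untouched, and no outpatient admission data need be lost, because the hospitalisation question is not restricted. This stands too and limits the severity.

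None of it removes the contradiction. An unseen analysis plan would not settle it either, because the article does not leave the analysis open. It states a specific one that conflicts with its own objective.

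**Conclusion.** The analysis as written does not answer the stated secondary objective, because it excludes every participant enrolled as an outpatient and counts only readmissions. That conclusion rests on the text alone.

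The size is illustrative: about 11 events against about 3, and power of about 21% against about 9%, given 25% admission under usual treatment, a hazard ratio of 0.5, a 30% inpatient share and equal risk by modality. A reader might take this to mean that the correction yields an adequately powered comparison. It does not; at a hazard ratio of 0.5, power stays below 40% with all 58 participants even at a 40% event rate. The gain is that the analysis matches the objective and uses all randomised participants.

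Handling of the index stay is a secondary clarification. The point should be fixed before analysis, but it does not threaten the trial's primary result.

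**What to change.** 1. Fit the Cox model to all randomised participants by assigned arm, with time from randomisation to first new psychiatric admission for self-injurious behaviour, censored at loss to follow-up or end of study. State that continuation of the index stay is not an event.
2. Stratify the model by inpatient or outpatient status at entry.
3. Keep readmission among patients enrolled in hospital as a subgroup analysis, labelled as such.
4. Keep randomisation as the main time origin. If the index discharge date can be obtained, add a sensitivity analysis in which patients hospitalised at entry join the risk set at discharge, and note that discharge occurs after randomisation.
5. Use the same population and event in the objective, the outcome definition and the analysis, and describe the comparison as not confirmatory.

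The main cost is wording. Treatment modality is already collected, and hospitalisation is already asked of participants in both modalities. The timeline mentions the admission date only for the day-30 and day-60 calls, so confirm that it is also recorded at day 90. The index discharge date is not listed among the data collected; it is needed only for the sensitivity analysis, and its availability must be checked.

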### Safety procedure

A strict suicide safety protocol will be followed given our participant eligibility criteria. Patient safety will be the highest priority in this study. Included in the CALMA app’s “Emergency Card” is a linked directory of major crisis helplines and a geolocation feature of emergency services near the user’s location, allowing participants to connect directly to these services.

A suicide safety assessment will be carried out in each interview, where the SITBI will be administered. Under the circumstance that the patient is at risk, the interviewer (a psychiatric member of the research group) will alert the parent and indicate that he/she accompany the participant to the Emergency Department of the center where the recruitment was carried out to be evaluated by a mental health professional. The interviewer also will alert the study coordinator ([name]) and will alert the research collaborator at each recruitment center. Each collaborator will immediately notify to the emergency room physician on call that day for an acute psychiatric assessment so that said clinician can contact the participant’s parent, guaranteeing the presence of the patient in the emergency department. In addition, each collaborator will notify the patient’s pediatric medical team of each hospital.

